**8.1.3. Gel Imaging**

Gels will be scanned using the Typhoon 9410 imager (GE Healthcare), with a resolution of 100µm, and PMT of 500/600V.

**8.1.4. Gel Data Analysis**

Data obtained from the gels will be quantified using the DeCyder version 6.5 software (GE Healthcare). The Differential In-gel analysis (DIA) will be used to optimize spot detection, with the master gel being assigned automatically to the gels with most spots detected. The Biological Variation Analysis (BVA) module will be used for analysis of each sample according to the corresponding age-group. The filtering parameters will then be set to determine the spots that: had a p-value ≤ 0.05 for the t-test employed to test the variation between age-groups and a >1.5 fold change in abundance between the groups.

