From our previous work in a porcine heart transplant model significant myocardial protection could be achieved in the donor heart following transplantation into a preconditioned donor (9). The study ruled out the neurogenic mechanism of protection, as the transplanted heart was denervated, and suggested that remote IPC produces a blood-borne protective factor (9). This study also demonstrated that remote IPC induced a circulating factor in the blood that provided myocardial protection in transplanted heart. In other words, the remote IPC induced a lasting protected environment in the recipient prior to transplantation of the donor heart (i.e., the heart was not in the body during the IPC stimulus). This study suggested the presence of a humoral circulating factor in blood. We then further localized a “protective factor” and demonstrated in an animal model that remote IPC elaborated a transferable plasma-borne factor that protected mitochondrial structure and function and preserved myocardial performance following neonatal cardioplegic arrest (22). This metabolic and structural protection was associated with preservation of global myocardial performance (22). We have further studied human leukocyte functional responses in our pilot study performed in healthy human volunteers (24) and demonstrated that the remote IPC stimulus significantly decreased neutrophil adhesion, exocytosis, and phagocytosis. Our human pilot study (24) as well as our global genomic study (5) suggested that proteomic response to remote IPC stimulus will be significant. Others have also demonstrated that IPC can be abolished by inhibition of de novo protein synthesis at both transcription and translation levels (31-32). Furthermore, our previous genomic studies demonstrated significant changes in global gene expression in murine myocardium after the remote IPC stimulus (10) and in the human myocardium in children undergoing heart surgery (25). However, it remains unknown if the global genomic response observed in our previous studies results in translation of expressed genes into proteins. Over the recent year proteomic profiling has evolved as a reliable, reproducible and powerful technique of assessment of global protein expression in response to clinically relevant IR injury (33,34) and particularly CPB (35). This technique allows simultaneous assessment of expression of a great number of thematically linked proteins, including mitochondrial metabolic signalling proteins that may constitute protective pathways.

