**5.1.5 Blood sampling**

The following 5 blood samples (6.5 ml each) will be taken from the arterial line that is routinely placed in all patients: baseline, immediately after discontinuation of CPB, at 6, 12, and 24 hours following discontinuation of CPB. No additional lines or invasive procedures will be performed apart from those that routinely required for heart surgery. From each sample, 1.5 ml will be used for proteomic assays, and 5 ml for the lymphocyte mitochondrial function assays.

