**8.1.5. Spot Excision and Identification**

Proteins of interest (determined by change from baseline) will be excised robotically using the Ettan Spot-picker (GE Healthcare) and identified by tandem mass spectrometry (MS/MS) on an HPLC-Chip ESI-Trap XCT tandem mass spectrometer or LTQ-FT mass spectrometer. Protein identification will be verified with the use of western blots using specific antibodies.

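### The spot filter (per-spot p ≤ 0.05 and >1.5-fold) sets no limit on false calls across a global proteomic screen, and it is not worded for the RIPC-versus-sham contrast

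*Protocol*

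**What the plan says.** Protocol Section 8.1.4 (Gel Data Analysis) sets a two-part filter. A spot is kept if it "had a p-value ≤ 0.05 for the t-test" and shows "a >1.5 fold change in abundance between the groups". The t-test is described as "employed to test the variation between age-groups".

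Section 8.1.5 (Spot Excision and Identification) gives another basis for picking spots: "Proteins of interest (determined by change from baseline", with no threshold. It then says "Protein identification will be verified with the use of western blots using specific antibodies".

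The scope is wide. The Background section says of proteomic profiling: "This technique allows simultaneous assessment of expression of a great number of thematically linked proteins". Section 5.1.5 takes blood at "baseline, immediately after discontinuation of CPB, at 6, 12, and 24 hours following discontinuation of CPB", and adds "From each sample, 1.5 ml will be used for proteomic assays". Section 8.1.2 balances dyes within each time point.

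The primary objective and hypothesis in Section 3 include the global plasma proteomic response to RIPC. The primary outcome in Section 4 is the identification of molecular signalling in response to RIPC. Section 10.3 names ANOVA, the t test, stepwise regression and analysis of covariance. None of Sections 8.1.4, 8.1.5, 10.1 or 10.3 mentions a multiplicity adjustment, a false discovery rate or a validation set.

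**The concern.** A threshold of 0.05 per spot limits the error for one spot. It does not limit the number or share of false calls when the same test is run on every spot of a global screen, possibly at several times. A fold-change cut-off looks like extra protection, but how much it gives depends on how variable each spot is between children. For noisy spots it gives almost none.

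The protein list is part of the primary result. If its false share is unknown, a reader cannot tell candidates for a protective factor from noise. The later laboratory work does not settle this, because the western blot confirms which protein a spot contains. No repeat of the group comparison in independent patients is described.

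The contrast is a linked difficulty. This trial has two arms, sham and RIPC, and defines no age-groups. Read literally, the filter does not compare the randomised arms, and Section 8.1.5 selects on yet another basis. An error rate means little until the comparison it belongs to is stated.

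**Working it through.** **The plan's own figures.** The protocol gives no spot count, spot variability, expected number of false calls or proteomic power calculation. The only sample-size calculation in Section 10.1 with complete inputs is for mitochondrial oxygen consumption (difference 20%, SD 14.5, alpha 0.05, power 0.8). A two-sided t-test needs 9.32 per group, so 10, which matches the stated figure read as per group. That calculation concerns one endpoint at 0.05 and says nothing about a screen.

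**Inputs for the check.** From the protocol: 20 per group (Section 5.1.1), p ≤ 0.05 and fold change above 1.5 (Section 8.1.4), four post-bypass samples (Section 5.1.5). Assumed: the contrast is RIPC versus sham, the test is two-sided on log abundance, abundances are lognormal, CV is 0.2 to 1.0, and there are 500 to 1,500 spots. Testing at each time is inferred from Sections 5.1.5 and 8.1.2; Section 8.1.4 does not say so.

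**Step 1: p-value part alone, no true effect.** Expected false calls = 0.05 × spots × times.

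- One time: 0.05 × 500 = 25; 0.05 × 1,500 = 75.
- Four times: 4 × 25 = 100; 4 × 75 = 300.

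These are roughly upper bounds, since the fold filter can only remove spots.

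**Step 2: what the fold filter adds.** On the log scale the SD is s = √ln(1 + CV²), and the standard error of the difference in means is SE = s × √(2/20). The fold filter needs a difference above ln 1.5 = 0.405. The t-test needs a difference of about 2.024 × SE (38 degrees of freedom). The two cut-offs meet at SE = 0.405 / 2.024 = 0.200, which gives s = 0.633 and CV of about 0.70. Below that CV the fold filter is the stricter part; above it the p-value is, and the filter adds little.

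Example at CV 0.5: s = √ln 1.25 = 0.472, SE = 0.149, and 0.405 / 0.149 is about 2.71. The two-sided normal tail is about 0.0066, or 6.6 per 1,000.

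**Step 3: joint rule by simulation** (20 v 20, no effect; the ranges cover fold change taken as a ratio of geometric or of arithmetic means, and repeated runs).

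| Between-child CV (assumed) | Null spots passing, per 1,000 at one time | Same, four times (×4) |
|---|---|---|
| 0.3 or less | about 0 | about 0 |
| 0.4 | about 1 | about 4 |
| 0.5 | 6–9 | 24–36 |
| 0.7 | 32–36 | 128–144 |
| 1.0 | 44–50 | 176–200 |

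The same rule can therefore pass almost no null spots or nearly the full 5%. Nothing in the protocol says which applies, and spots on one gel set may differ in CV.

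**Step 4: does any later step limit the error?** Section 8.1.5 verifies identity by mass spectrometry and western blot. Section 10.3 lists covariate models and a check of the analyses by an independent statistician. Neither sets an error rate for the list.

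**The case against.** The strongest reply is that this is a discovery screen. The criteria are called filtering parameters, they precede excision and identification, and the primary outcome also covers mitochondrial function and signalling in heart muscle. A screen may tolerate false leads, and the fold filter may remove nearly all of them if CVs are about 0.3. A separate analysis plan might also add error control.

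Much of this stands. Exploratory labelling with later confirmation would be legitimate, but the protocol does not apply that label; it places the proteomic response in the primary hypothesis. The threshold is written into the protocol itself, so this is not merely a detail left for a later plan. The low-CV case is possible but is not documented.

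A reader might infer three stronger things that the documents do not support. The first is that 5% of all spots will be falsely called; that ignores the second criterion. The second is that a list must appear even if RIPC does nothing; at CV 0.3 or less the joint rule would usually yield none. The third is that the rule as worded declares RIPC proteins; it names age-groups instead. Separate tests at all four times are also only one reading, since Section 10.3 mentions two-way ANOVA too. Within a single time the multiplicity over spots remains.

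**Conclusion.** The concern holds in a conditional form. Section 8.1.4 fixes an unadjusted per-spot rule for a global screen that feeds the primary outcome, and nothing in the protocol limits its false calls. The expected number ranges from about 0 to about 50 per 1,000 null spots per time, for assumed CVs up to 1.0. It is negligible at CV 0.3 or less and material from about 0.5 upward. Because spot count and CV are not given, the false share of the list cannot be stated. The figures rest on lognormal abundances, 20 per group and a RIPC-versus-sham reading of the test. The undefined age-groups, and the different selection basis in Section 8.1.5, must be corrected at the same time; otherwise any error control would attach to the wrong comparison.

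**What to change.** 1. In Section 8.1.4, replace the age-group wording with RIPC versus sham at named post-bypass times, for example on change from baseline, and make Section 8.1.5 select on the same contrast.
2. Replace p ≤ 0.05 with Benjamini-Hochberg control of the false discovery rate at 5% over all matched spots and those times.
3. Report the q-value, the estimated fold change and its 95% CI for each declared spot. Use fold change only to rank spots for excision.
4. Label any spot selected without this control as exploratory, and say that the western blot confirms identity only.

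The samples, gels and laboratory work do not change. The contrast and times have to be written down first, so this is slightly more than a one-line edit.

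The price is a shorter list of declared proteins and lower power per spot than at 0.05. As an illustration, if 10% of tests are declared, the Benjamini-Hochberg cut-off is 0.05 × 0.10 = 0.005. For a true 1.5-fold change at CV 0.5 with 20 per group, t-test power falls from 0.75 at 0.05 to 0.41 at 0.005. The actual loss depends on the unknown CVs and on the share of spots that truly change.

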# STUDY OBJECTIVES

- 1. **Primary Objective**

Does remote IPC modify the global plasma proteomic and mitochondrial response in patients undergoing congenital heart surgery?

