**Hypothesis:**

Remote IPC induces significant changes to global proteomic response in plasma and the metabolic function in heart muscle and lymphocyte mitochondria of patients undergoing congenital heart surgery.

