**5.1.1 Description**

The hypothesis will be tested in children with tetralogy of Fallot undergoing elective open heart surgery with standard heart arrest and cardiopulmonary bypass. An informed consent will be obtained from all the patients’ parents or guardians. 40 patients will be recruited in to the study within two years. They will be randomized into 2 equal sized groups: Group I control (Sham, n=20) and Group II preconditioning (RIPC, n=20).

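### Section 8.1.4 filters the gel spots by age-group, which the protocol never defines, so as written the filter does not test RIPC against sham

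*Protocol*

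**What the plan says.** The primary objective asks: "Does remote IPC modify the global plasma proteomic and mitochondrial response in patients undergoing congenital heart surgery". The matching hypothesis begins "Remote IPC induces significant changes to global proteomic response in plasma". Section 5.1.1 creates two arms of 20, sham control and RIPC.

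Section 8.1.4 (Gel Data Analysis) names another grouping factor twice. The Biological Variation Analysis module is for "analysis of each sample according to the corresponding age-group", and spots are then kept if p ≤ 0.05 "for the t-test employed to test the variation between age-groups" and the abundance differs by more than 1.5-fold between the groups. In that sentence the groups can only be the age-groups.

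Section 8.1.5 (Spot Excision and Identification) gives a second rule: "Proteins of interest (determined by change from baseline) will be excised robotically".

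Section 10.3 lists an unpaired t-test or two-way ANOVA without naming factors or mentioning gel spots. It treats age as one of several possible influences to be examined by regression or analysis of covariance.

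**The concern.** The filter in 8.1.4 decides which spots count as different. If it compares age-groups, a protein passes because it varies with age, or by chance, and not because RIPC changed it. Eligible ages run from one month to 18 years, so age differences in plasma proteins are plausible. The protocol gives no cut-point, so the stated test cannot even be set up without inventing one. If the contrast is instead corrected once the gel data are in hand, the comparison for half of the primary question will have been chosen after the fact.

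**Working it through.** **1. Which groups exist.**

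| Place in protocol | Grouping or comparison |
|---|---|
| Primary objective and hypothesis | effect of RIPC |
| 5.1.1 | sham (20) and RIPC (20) |
| Eligibility Criteria | one age range, one month to 18 years, no bands |
| Randomisation Procedures | not stratified |
| 8.1.4 | age-group, for both the analysis and the filter |
| 8.1.5 | change from baseline, no arms named |
| 8.2.4 (MPTP assays) | sham control and RIPC groups |
| 10.3 | age as a possible influence; factors of the tests not named |

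The text of section 8.1 never states a RIPC-versus-sham comparison. Section 8.2.4 does, so the defect is confined to the proteomic part.

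**2. The plan's own figure, for scale.** Section 10.1 gives at least 10 subjects for a 20% difference in mitochondrial oxygen consumption (sigma 14.5, alpha 0.05, power 0.8, two groups). Assume that 20 and 14.5 are on one scale and the test is two-sided. Then n per group = 2 × (1.960 + 0.842)² × (14.5/20)² = 2 × 7.85 × 0.526 = 8.25, rounded up to 9. The exact t-test gives 9.32, rounded up to 10. The figure reproduces as 10 per group. It is used here only for its standardised effect, d = 20/14.5 = 1.38. With 20 per arm, 80% power is reached at d = 0.91.

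**3. What the age-group t-test detects.** Suppose RIPC shifts a protein by d and age has no effect on it. The expected difference between two age-groups is d × (share on RIPC in group 1 − share on RIPC in group 2). Randomisation makes that bracket zero on average.

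This was checked by simulation: 40 patients, 20:20, age-group independent of arm, no age effect, two-sided 0.05. There were 40,000 runs for the age-group test and 3,000 for the arm test. The age splits are assumptions, since the protocol gives none.

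| Age split | Test | d = 0 | d = 0.91 | d = 1.38 | d = 2.0 |
|---|---|---|---|---|---|
| 20/20 | age-group | 4.9% | 5.0% | 4.9% | 5.0% |
| 20/20 | arm | 5.0% | 79.8% | 99.0% | 100% |
| 12/28 | age-group | 4.9% | 4.8% | 5.0% | 5.1% |
| 12/28 | arm | 4.6% | 80.4% | 98.5% | 100% |
| 8/32 | age-group | 4.8% | 5.0% | 4.8% | 5.1% |
| 8/32 | arm | 5.1% | 80.6% | 98.8% | 100% |

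The age-group test rejects at about 5% whatever RIPC does. The simulation covers the t-test alone. The >1.5-fold condition must hold as well, so it can only lower that rate.

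**4. Whether swapping the label is enough.** Section 8.1.2 makes each gel's internal standard from the two samples on that gel and assigns samples to gels at random. Take a multiplicative RIPC effect f, and assume all 40 samples at one time point are paired at random.

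- A gel with one sample per arm keeps the full log difference, because the shared standard cancels.
- A gel with two samples from one arm loses it, because f is in both the sample and its standard.
- The chance that a sample's partner comes from the other arm is 20/39 = 0.51.

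Pooled over gels, the expected log difference is therefore 0.51 × log f. A true 1.5-fold change would appear as 1.5^(20/39) = 1.23-fold. A true change of 1.5^(39/20) = 2.2-fold would be needed to show as 1.5. The arm comparison must allow for this.

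**The case against.** The strongest reply is that this is a slip of wording. With no age-groups defined, the test cannot be run as written, and the Research Question, the two randomised arms and the n = 20 per group in 10.1 all point to RIPC versus sham. That is probably what was meant. But 8.1.4 is the only specific rule for the spots, it names age-group twice, and the general list in 10.3 does not override it. Figure 3, to which section 8.1 refers for the proteomic strategy, is not shown and may name the arms. If it does, it conflicts with the text, which still needs correcting.

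A reader might infer more than the documents support:

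- **That the primary question as a whole cannot be answered.** It also has a mitochondrial part, and 8.2.4 names the sham and RIPC groups there.
- **That 8.1.5 picks only what bypass changes in both arms.** It does not say that change from baseline is pooled over arms, and such change is a natural measure of response to surgery. The fair criticism is that it names no arms and is not reconciled with 8.1.4.
- **That a protein changed by RIPC alone would be missed altogether.** This holds only if 8.1.4 must be passed before excision, which is not stated. Under 8.1.5 such a protein could still be picked.
- **That an age contrast in this trial would carry no RIPC signal at all.** Age balance holds only in expectation. With 40 unstratified patients, 12 of 20 on RIPC in one age-group and 8 of 20 in the other would carry 0.2d into the contrast. The 5% is an average over such imbalances.

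**Conclusion.** Section 8.1.4 is wrong as written. Its filter compares undefined age-groups and does not test the RIPC effect, so it does not answer the proteomic part of the primary question. For a protein affected only by RIPC, the age-group t-test is passed at no more than about 5% on average, against roughly 80% to 99% for the arm comparison at d = 0.91 to 1.38. These rates assume age independent of arm, no age effect on the protein, 20 per arm and a two-sided test. The arm-test power also assumes abundances comparable across gels. The conflict between 8.1.4 and 8.1.5 is a matter of reconciliation.

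**What to change.** - **8.1.4:** replace age-group by randomised arm in both places, so that the t-test and the >1.5-fold filter compare RIPC with sham at each post-CPB time point (end of CPB, 6, 12 and 24 hours). Keep age as a covariate, as 10.3 foresees. Coded group labels in the software would preserve the blind.
- **8.1.5:** select spots on that between-arm result. The between-arm difference in change from baseline is an alternative only if the baseline sample is confirmed to precede the cuff cycles. Sections 5.1.2 and 5.1.5 do not state the order.
- **8.1.2:** state how abundances are made comparable across gels, or make the comparison within gels carrying one sample from each arm.

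The cost is rewording two paragraphs and regrouping samples in the software. If the gel pairing or the internal standard changes, that must be settled before the gels are run, and within-gel pairing by arm needs someone who holds the allocation codes. No new patient samples are needed.

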# SUBJECT ENROLLMENT AND RANDOMISATION

- 1. **Recruitment**

Patients will be recruited by either the surgeon ([name]) or cardiologist ([name]) at the preadmission clinic or on the ward prior to surgery. The clinician ([name]/[name]) will explain to the patient’s parents/guardians, the research project, their child’s role, and outcomes and will obtain signed consent if granted.

- 1. **Eligibility Criteria**
     1. **Inclusion Criteria**

Patients with tetralogy of Fallot aged one month and older (to 18 years) having surgery for the first time.

- - 1. **Exclusion Criteria**

Patients with chromosomal defects, associated congenital lung malformations and haematological disorders will be excluded.

- 1. **Randomisation Procedures**

Random allocation is made in blocks in order to keep the sizes of the 2 treatment groups similar. In order to avoid predictability, the block size that is randomly selected is 2, 4 or 5, as the sample size must be divisible by the block size. Due to the expected relative uniformity of condition in the patient group and the small number of subjects the design will not be stratified. The randomisation will be performed in secret by a member from Heart Research (not involved in working for the trial) using SPSS statistical software generated randomisation and will place each designation sequentially in numbered envelopes 1 to 40, for patient 1 to 40 and the envelopes will be signed and sealed. The implementer of the RIPC or Sham co ntrol treatment protocols will open one envelope in numerical order immediately prior to placement of the blood pressure cuff and they will apply the RIPC treatment or sham control protocol accordingly.

- 1. **Blinding Arrangements**

[name] will not be blinded as she will be applying the RIPC treatment. She will also be involved in randomisation, sample collection, data collection, data entry and laboratory analysis. Surgeons, perfusionists, anaesthetists will be blinded. Samples will be de-identified and therefore, research laboratory staff will be blinded to the patient’s identity. The blood pressure cuff will be positioned on the thigh for both sham control and RIPC groups, however if other theatre staff witness whether the RIPC treatment protocol is invoked they will not be blinded. As these theatre staff are strictly performing standard clinical tasks and procedures and are not involved in the trial and analysis *per se*, this should not impact the blinding.

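### The gel-data filter in section 8.1.4 groups and tests samples by undefined age-groups, so as written it does not compare RIPC with sham

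*Protocol*

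**What the plan says.** Section 8.1.4 of the protocol (Gel Data Analysis) names age twice as the grouping factor. The Biological Variation Analysis module is to be used for "analysis of each sample according to the corresponding age-group". The filter that follows sets a p-value limit of 0.05 and describes its comparison in these words: "the t-test employed to test the variation between age-groups and a >1.5 fold change in abundance between the groups".

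The design has different groups. Section 5.1.1 states: "They will be randomized into 2 equal sized groups: Group I control (Sham, n=20) and Group II preconditioning (RIPC, n=20". The hypothesis under the primary objective is about treatment: "Remote IPC induces significant changes to global proteomic response in plasma".

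Two other sections bear on the gel data. Section 8.1.5 defines the proteins to be excised and identified as those that change from baseline. Section 10.3 lists two-way ANOVA or an unpaired t test for the study's analyses, with regression and analysis of covariance to examine the influence of age and other factors.

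**The concern.** Section 8.1.4 fixes the test, the p-value threshold, the fold-change cut and the software module, but attaches them to a factor that the trial neither randomises nor defines. A between-age comparison answers a different question from the one in the primary objective, and the plasma proteome is one of the two parts of that objective. An analyst who follows the section must either stop, because there are no age cut-points, or invent groups in a sample that may run from one month to 18 years. In the second case the filtered spots would describe age differences, and the filter would have no designed sensitivity to RIPC.

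This is not a detail left to a later analysis plan. The protocol states the rule, and states it with the wrong factor.

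**Working it through.** **1. Which factor each section names**

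| Protocol section | What it fixes | Factor or contrast |
|---|---|---|
| 3.1 Primary objective, hypothesis, aim | Plasma proteomic response | Effect of RIPC |
| 5.1.1 Description | Groups | Sham 20, RIPC 20 |
| 6, Eligibility | Age | One continuous range, no cut-points |
| 6, Randomisation | Stratification | None |
| 8.1.4 Gel Data Analysis | Sample grouping, t test, fold change | Age-group |
| 8.1.5 Spot Excision | Proteins to identify | Change from baseline |
| 10.3 Statistical Analysis Plan | Tests for the study in general | Not named; age is a possible influence |

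On age, eligibility reads "Patients with tetralogy of Fallot aged one month and older (to 18 years) having surgery for the first time". On stratification, the protocol says that, given the expected uniformity of the patients and "the small number of subjects the design will not be stratified". Neither creates age-groups.

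The fold-change clause in 8.1.4 refers to the groups without qualification, but the only groups named in that paragraph are the age-groups. Age-group also occurs in the preceding sentence, so this is not one stray word. Section 8.2.4 does name sham and RIPC, but only for the mitochondrial pore experiments.

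**2. Size, as an illustration**

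The protocol has no figure of its own to reproduce here. Section 10.1 gives a 10-20% sensitivity for mitochondrial proteins, with no SD, alpha or power for the proteomic comparison.

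From the protocol: 20 per arm, p ≤ 0.05, fold change above 1.5. Assumed: two-sided test, between-child SD 0.5 on the log2 scale (range 0.4 to 0.7), two equal age groups of 20 unrelated to arm, and a true RIPC effect of exactly 1.5-fold.

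- Effect: log2(1.5) = 0.585.
- Standard error of a difference between two groups of 20: 0.5 × √(2/20) = 0.158.
- Noncentrality by arm: 0.585 / 0.158 = 3.70. Critical t on 38 degrees of freedom: 2.02.
- Power by arm, p-value only: 95.0% (99.5% at SD 0.4, 73.1% at SD 0.7).
- Both criteria by arm: about 50%. At SD 0.5, p ≤ 0.05 needs an observed log2 difference of about 2.02 × 0.158 = 0.32, below the 0.585 that the fold filter needs. The fold filter therefore decides, and a true effect lying on the cut exceeds it half the time. The same holds at SD 0.4 and 0.7.
- By age-group, simulated: p ≤ 0.05 in about 5% of trials, which is alpha; both criteria in about 0.1%.

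| SD 0.5, true 1.5-fold RIPC effect | Tested by age-group | Tested by arm |
|---|---|---|
| p ≤ 0.05 | about 5% | 95% |
| p ≤ 0.05 and >1.5-fold | about 0.1% | about 50% |

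A second simulation, with an effect of 0.91 SD (80% power at 20 per arm), gave 80.1% by arm and 5.1% by age-group.

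**The case against.** The strongest reply is that 8.1.4 is a laboratory-methods paragraph and that inference belongs to 10.3. That section sends laboratory values from coded samples to statistical testing once the assays are complete, and lists an unpaired t test and two-way ANOVA. Sections 5.1.5 and 10.1 both call the proteomic work assays, so 10.3 can be read to cover it. With only two groups in the design and a primary question about RIPC, the intended contrast is hardly in doubt. This stands in part: a reader might infer that the trial never tests RIPC against sham on the proteome, and the protocol does not support going that far. But 10.3 names neither the proteome nor the contrast, so it does not correct the specific instruction in 8.1.4.

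The second reply is that the age filter may not decide which proteins are identified, since 8.1.5 selects by change from baseline. This also stands. A reader might infer that the final protein list would be a list of age-related proteins; with two unreconciled selection rules, that is not established. Change from baseline is not a between-arm contrast either, so 8.1.5 does not repair the gap.

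Third, the age-group test cannot be run without invented cut-points, so the practical effect may be ambiguity, not a test silently run on the wrong factor. That is fair, and it is why the percentages above are only an illustration.

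**Conclusion.** The point holds in a limited form. Section 8.1.4 names an undefined factor where the randomised groups belong, and the only explicit between-group comparison for the gel data is therefore not RIPC versus sham. This follows from the text alone and needs no assumption.

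The size rests on an SD, an effect and an age split that the protocol does not give. It largely restates that a test on a factor unrelated to treatment detects a treatment effect at about the rate of alpha. The fair comparisons are 5% with 95% on the p-value alone, and 0.1% with 50% on both criteria. A reader might set 0.1% against 95%, or say that a true 1.5-fold age effect would be flagged 95% of the time. Neither is right, because the filter requires both criteria and an effect on the cut passes both only about half the time.

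The sampling and assays are unaffected. Because the passage governs part of the primary objective, it should be corrected before any gel data are analysed.

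**What to change.** In section 8.1.4, replace both references to age-groups with the randomised groups, RIPC versus sham, for the module's grouping and for the t test and fold-change filter. State which sampling time, or which change from baseline, is compared. The protocol has a baseline sample and four post-bypass samples and does not say which of them the filter uses; testing every post-bypass time would mean four tests per spot, and should be a deliberate choice.

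Align section 8.1.5 so that its selection rule follows from the same contrast, and have section 10.3 name the proteomic comparison and its factors. Age stays as a covariate under 10.3.

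The cost is a short wording change in 8.1.4 and a matching line in each of the other two sections, with no extra patients, samples or assays.
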